## Abstract

**Background:**

Fractures of the proximal humerus are associated with a profound temporary and sometimes permanent, impairment of function and quality of life. The treatment of comminuted fractures of the proximal humerus like selected three-or four-part fractures and split fractures of the humeral head is a demanding and unresolved problem, especially in the elderly. Locking plates appear to offer improved fixation; however, screw cut-out rates ranges due to fracture collapse are high. As this may lead to higher rates of revision surgery, it may be preferable to treat comminuted fractures in the elderly primarily with a prosthesis or non-operatively. Results from case series and a small-sample randomized controlled trial (RCT) suggest improved function and less pain after primary hemiarthroplasty (HA); however these studies had some limitations and a RCT is needed. The primary aim of this study is to compare the Constant scores (reflecting functional outcome and pain) at one year after primary HA versus non-operative treatment in elderly patients who sustained a comminuted proximal humeral fracture. Secondary aims include effects on functional outcome, pain, complications, quality of life, and cost-effectiveness.

**Methods/Design:**

A prospective, multi-center RCT will be conducted in nine centers in the Netherlands and Belgium. Eighty patients over 65 years of age, who have sustained a three-or four part, or split head proximal humeral fracture will be randomized between primary hemiarthroplasty and conservative treatment. The primary outcome is the Constant score, which indicates pain and function. Secondary outcomes include the Disability of the Arm and Shoulder (DASH) score, Visual Analogue Scale (VAS) for pain, radiographic healing, health-related quality of life (Short-form-36, EuroQol-5D) and healthcare consumption. Cost-effectiveness ratios will be determined for both trial arms. Outcome will be monitored at regular intervals over the subsequent 24 months (1, 3 and 6 weeks, and 3, 6, 12, 18, and 24 months). Data will be analyzed on an intention to treat basis, using univariate and multivariable analyses.

**Discussion:**

This trial will provide level-1 evidence on the effectiveness of the two mostly applied treatment options for three-or four part and split head proximal humeral fractures in the elderly. These data may support the development of a clinical guideline for treatment of these traumatic injuries.

**Trial registration:**

Netherlands Trial Register (NTR2040).

## Background

Fractures of the proximal humerus are one of the most frequently encountered fractures in the elderly. The incidence is approximately 66 per 10,000 person years [1]. Most of these fractures are treated non-operatively and careful early motion with varying results. Especially, the treatment of three-or four-part fractures and split head humeral fractures is an unresolved problem [1-4].

Locking plates have been used during the last decade. They appear to offer improved fixation, however at considerable rates of complications such as non-union, malunion, or complaints of hardware (e.g., impingement). Also, the prevalence of screw cut-out ranges from 11 to 43% due to osteoporosis and avascular necrosis of the humeral head [5]. According to Hertel et al. [6] fractures of the proximal humerus involving the anatomical neck are mostly at risk for developing ischemia. Therefore, primary hemiartroplasty may be preferable over locking plates for these specific fracture types in the elderly.

Primary hemiarthroplasty and non-operative treatment of comminuted proximal humeral fractures have been described in a number of studies with varying functional results [7-15]. Up till now, only one RCT comparing HA with non-operative treatment has been published; less pain and better overall function was reported for the HA group (N = 32 patients) [13]. However, due to methodological limitations (e.g., indistinct inclusion criteria and differences in age at baseline) the outcome of this RCT may not be generalizable. A properly designed RCT is needed in order to gain insight into the best treatment for those comminuted proximal humeral fractures that are mostly at risk for avascular necrosis.

### Study objectives

The primary aim of this study is to compare the Constant score, reflecting functional outcome and pain, after primary hemiarthroplasty (HA) versus non-operative treatment in patients over 65 years of age who sustained a comminuted fracture of the proximal humerus.

Secondary aims are to determine the effect of primary HA versus non-operative treatment on the degree of disabilities of the arm, shoulder and hand (DASH score), level of pain (VAS), the rate of secondary interventions, complications and mortality, the radiographic healing, and the health-related quality of life (Short-Form 36, SF-36, and EuroQol-5D, EQ-5D) in these patients. Finally, upon calculation of the costs for both the HA and the non-operative groups, the cost-effectiveness of these treatments will be determined and compared.

Based upon limited literature data available, our main study hypothesis is that HA will result in higher Constant scores (reflecting better functional outcome with less pain) at 1 year compared with non-operative treatment of comminuted proximal humeral fractures in the elderly Despite higher initial costs, it is expected that HA will be more cost-effective than conservative treatment.

## Methods/Design

### Study design

The ProCon trial will follow a multicenter randomized controlled trial design. Eight centers in the Netherlands and one in Belgium will participate. The study started June 15, 2009. The trial has been designed in accordance with de Declaration of Helsinki (59th World Medical Association General Assembly, Seoul, October 2008) [16] and in accordance with the Medical Research Involving Human Subjects Act. It will follow the CONSORT (CONsolidation of Standards of Reporting Trials) guidelines [17,18].

### Recruitment and consent

Eligible persons presenting to the Emergency Department (ED) with a comminuted proximal humeral fracture will be informed about the trial at the ED. They will receive information and a consent form from the attending physician, the clinical investigator or a research assistant. After providing written informed consent, eligible patients will be randomized to two treatment strategies. Variable block randomization will be accomplished via a trial website. Allocation will be at random. Follow-up will take place over a period of two years.

### Study population

All persons aged 65+ who present at the Emergency Department with a comminuted fracture of the proximal humerus are eligible for inclusion. Presence of a proximal humeral fracture can be confirmed on X-ray, however fracture classification requires 3-dimensional Computed Tomography (CT) reconstructions [6,19].

Patients meeting the following inclusion criteria are eligible for enrolment:

1. Adult men or women aged 65 years and older (with no upper age limit)

2. Fracture of the humeral head

3. Selected three-part (Hertel classification type 9, 10, 11), selected four-part (Hertel type 12), anatomical neck (Hertel type 2), or split-head fractures of the humeral head in the judgement of the attending surgeon. All fractures should be classified according to the binary description system, based on 3D CT reconstructions (Figure 1 and 2)

**Figure 1 F1:**
[figure not shown]
**Binary (LEGO) description system of the Hertel classification of proximal humerus fractures**. The 12 basic fracture patterns result after combining the 5 basic fracture planes. Basic fracture planes lie between the greater tuberosity and the head, the greater tuberosity and the shaft, the lesser tuberosity and the head, the lesser tuberosity and the shaft, and the lesser tuberosity and the greater tuberosity. There are 6 possible fractures dividing the humerus into two fragments, 5 possible fractures dividing the humerus into three fragments, and a single fracture dividing the humerus into four fragments Categories eligible for enrolment into the current trial are indicated in red boxes. **Reprinted from J Shoulder Elbow Surg, 13, Hertel R, Hempfing A, Stiehler M, Leunig M: Predictors of humeral head ischemia after intracapsular fracture of the proximal humerus, pp 427-433, with permission from Elsevier**.

**Figure 2 F2:**
[figure not shown]
**Head-split components**. Classic head-split geometry (left) and special head-split geometry where both fragments remain perfused (right). Categories eligible for enrolment into the current trial are indicated in red boxes. **Reprinted from J Shoulder Elbow Surg, 13, Hertel R, Hempfing A, Stiehler M, Leunig M: Predictors of humeral head ischemia after intracapsular fracture of the proximal humerus, pp 427-433, with permission from Elsevier**.

4. Operative treatment within 21 days (if randomized for HA)

5. Provision of informed consent by patient

6. Assurance that the surgeon who will perform HA has attended the pre-trial HA course (Erasmus MC Skills lab)

If any of the following criteria applies, patients will be excluded:

1. Polytrauma patients

2. Patients with an additional traumatic injury of the affected arm

3. Patients with a pathological, recurrent or open humerus fracture

4. Patients with an impaired shoulder function (i.e., stiff or painful shoulder, neurologic disorder of the upper limb, or diagnosed rotator cuff impairment) prior to the injury

5. Retained hardware around the affected humerus

6. Patients with a disorder of bone metabolism other than osteoporosis (e.g., Paget's disease, renal osteodystrophy, osteomalacia)

7. Moderate or severe cognitively impaired patients (i.e., Mini-Mental Status Examination (MMSE) Six Item Screener with 3 or more errors)

8. Likely problems, in the judgment of the investigators, with maintaining follow-up (e.g., patients with no fixed address will be excluded)

9. Insufficient comprehension of the Dutch language to understand a rehabilitation program and other treatment information in the judgment of the attending physician

The Six Item Screener for dementia (exclusion criterion 7) is a brief and reliable instrument for identifying subjects with cognitive impairment. The patient is asked to remember three words (e.g., apple, table, penny), then to say the day of the week, month, year, and finally to recall the three words without prompts. Using a cut-off of 3 or more errors, the sensitivity and specificity of the Six Item Screener for diagnozing dementia was 88.7 and 88.0, respectively [20].

Exclusion of a patient because of enrolment in another ongoing drug or surgical intervention trial will be left to the discretion of the attending surgeon, on a case-by-case basis.

### Interventions

Patients will be randomized to either hemiarthroplasty or conservative treatment.

Hemiarthroplasty (Figure 3A) will be performed using the Affinis^® ^Fracture shoulder endoprosthesis (Mathys AG Bettlach). No other prosthesis types will be used in order to increase homogeneity of data. Critical steps of the surgical procedure will be standardized. Standardized items will include the positioning of the patient (i.e., beach-chair position, with the scapula supported) and anesthesia (i.e., general or interscalene nerve block), surgical approach (a modified lateral deltoid split approach), exposure, shaft preparation, stem placement and cementing, and fixation of the tubercles with a cable wire [21]. After surgery, patients are allowed to use a sling for two days to one week. Patients will receive after-treatment following a standardized protocol, developed by an experienced physical therapist (Dept. of Rehabilitation and Physical Therapy, Erasmus MC, Rotterdam, The Netherlands). Anteflexion and elevation exercises may be started immediately if tolerated. Rotation exercises against resistance are not allowed during the first six weeks after surgery. Physical therapy sessions will be held at regular intervals, preferably two times a week during 12 weeks. The exact frequency and duration of physical therapy will largely depend upon the extent of functional recovery. This will be left at the discretion of the therapist.

**Figure 3 F3:**
[figure not shown]
**Examples of proximal humerus fracture, managed by endoprosthesis (A) or conservative treatment (B)**.

In order to ensure similar peri-operative regimens, participating centers will standardize the following key aspects of pre-and post-operative care. Pre-operatively, patients will receive antibiotic prophylaxis (single dose) and thromboprophylaxis, and their condition prior to surgery will be optimized if necessary. Post-operatively, patients will receive thomboprophylaxis during hospital stay (e.g., unfractionated heparin, Low Molecular Weight Heparin (LMWH), or equivalent). Surgical delay and physical therapy and rehabilitation programs be recorded but not standardized.

Conservative treatment (Figure 3B) is defined by treatment with a collar and cuff for three weeks. After one week circumduction exercises will start under supervision of a physical therapist. At three weeks after trauma, full range of motion excercises will be initiated if tolerated. Physical therapy sessions will be held at regular intervals, preferably two times a week during 12 weeks. The exact frequency and duration of physical therapy will largely depend upon the extent of functional recovery. This will be left at the discretion of the therapist. Details of the therapy program will be recorded.

### Pre-trial hemiarthroplasty course

In order to ensure that all participating surgeons perform the surgical procedure in a similar manner, they will attend a one-day technique-oriented training prior to the commencement of the trial. The training will be held at the Surgical Skills Lab (Erasmus MC, Rotterdam, the Netherlands) and will be given by experienced surgeons ([name], [name], SN). The surgical procedure will be practiced on human cadavers, with main focus on the critical aspects of the surgery including surgical approaches and implant-related insertion guidelines for the implant used. A refresher course will be planned after 6 months in order to ensure that sufficient knowledge is maintained. After each operation, surgeons will have to complete a surgical report form, in which space will be provided to report deviations, if any. Two experts ([name] and [name]) will judge if surgery has been performed as intended and, if not, they will directly provide feedback to the surgeon.

### Outcome measures

The primary outcome measure will be the Constant score. This scoring system consists of four variables, reflecting both function and pain of the shoulder joint [22]. The subjective variables are pain (15 points), activities of daily living (ADL; i.e., sleep, work, recreation/sport; 10 points), and arm positioning (10 points), which give a total of 35 points. The objective variables are range of motion (ROM; 40 points) and strength (25 points), which give a total of 65 points. ROM includes forward flexion (10 points), lateral elevation (10 points), external rotation related to the head (10 points) and internal rotation related to the spine column (10 points). Forward flexion and lateral elevation are measured using a goniometer. Strength of abduction will be measured using a calibrated spring balance. The right and left shoulders will be assessed separately.

Secondary outcome measures are:

- Disabilities of the Arm, Shoulder and Hand (DASH) score

- Visual Analogue Scale (VAS) for pain

- Rates of secondary interventions

- Radiographic healing

- Mortality rate

- Complication rates

- Health-related quality of life: Short Form-36 (SF-36)

- Health Utility: EuroQol-5D (EQ-5D)

- Healthcare consumption (for cost calculations)

- Cost-effectiveness

The Disabilities of the Arm, Shoulder and Hand (DASH) Outcome Measure is a validated 30-item, self-report questionnaire designed to help describe the disability experienced by people with upper-limb disorders and also to monitor changes in symptoms and function over time [23-25]. The DASH outcome measure is scored in two components: the disability/symptom section (30 items, scored 1-5) and the optional high performance Sport/Music module (4 items, scored 1-5). The DASH disability/symptom score is a summation of the responses to 30 questions on a scale of 1 to 5. Scores may range from 0 points (no disability) to 100 points (severe disability). The questions test the degree of difficulty in performing a variety of physical activities because of arm, shoulder, or hand problems (21 items). They also investigate the severity of pain, activity-related pain, tingling, weakness, and stiffness (5 items), as well as the effect of the upper limb problem on social activities, work, sleep, and self-image (4 items).

Pain level will be determined using a 10-point Visual Analog Scale, in which 0 implies no pain and 10 implies the worst imaginable pain.

Secondary interventions within one year of initial treatment to promote fracture healing, relieve pain, treat infection, or improve function include the following:

1. (Reversed) Arthroplasty placement (conservative group only)

2. Plate fixation (conservative group only)

3. Incision and drainage for superficial surgical site infection (HA group only)

4. Incision and drainage for deep surgical site infection (HA group only)

5. Revision to Affinis^® ^Reversed prosthesis (HA group only)

6. Implant exchange (HA group only)

7. Implant removal (HA group only)

Radiographic healing will be determined using CT scanning at one year. Location and consolidation of the tubercles will be scored in duplicate by two experienced surgeons ([name] and [name]). In case of differences between them, they will discuss the images until they reach an agreement.

Complications: complication rates in the HA group may include infection, neurovascular injury, malpositioning of the prosthesis, asceptic loosening of the prosthesis, dislocation of the tubercles. Complication rates in the control group may include malunion, nonunion, secondary dislocation, and symptomatic avascular necrosis of the humeral head.

The Short-Form 36 is a validated multi-purpose, short-form health survey with 36 questions, representing eight health domains that are combined into a physical and a mental component scale [26]. The Physical Component Scale (PCS) combines the health domains physical functioning (PF; 10 items), role limitations due to physical health (RP; 4 items), bodily pain (BP; 2 items), and general health perceptions (GH; 5 items). The Mental Component Scale (MCS) combines the health domains vitality, energy, or fatigue (VT; 4 items), social functioning (SF; 2 items), role limitations due to emotional problems (RE; 3 items), and general mental health (MH; 5 items). Scores ranging from 0 to 100 points are derived for each domain, with lower scores indicating poorer function. These scores will be converted to a norm-based score and compared with the norms for the general population of the United States (1998), in which each scale was scored to have the same average (50 points) and the same standard deviation (10 points).

The EuroQol (EQ-5D) is a validated and extensively used general health questionnaire to measure quality of life [27,28]. It is recommended for the assessment of QoL in trauma patients, especially for economic assessments [29,30]. EQ-5D has been developed by the EuroQoL Group in order to provide a simple, generic measure of health for clinical and economic appraisal [31]. EQ-5D consists of the EQ-5D descriptive system and the EQ Visual Analog Scale (EQ VAS). The EQ-5D descriptive system comprises five dimensions: mobility, self-care, usual activities, pain/discomfort, and anxiety/depression. Each dimension is marked as either no problems, some problems, or severe problems, which results in a 1-digit number expressing the level selected for that dimension. The digits for five dimensions are combined in a 5-digit number describing the respondent's health state. The EQ VAS records the respondent's self-rated health on a vertical, visual analog scale. Scores ranging from 0 ('Worst imaginable health state') to 10 ('Best imaginable health state') can be used as a quantitative measure of health outcome as judged by the individual respondents.

Cost measurement will be in accordance with Dutch guidelines for economic evaluations. Healthcare consumption data will be collected using a custom-made questionnaire. Health care costs will include costs of general practice care, medical specialist care, physical therapy, hospitalization, medication, home care, and other costs directly associated with diagnosis, treatment and rehabilitation. Where possible standard cost prices will be used as published by Oostenbrink will be used [32]. In accordance with guidelines for differential discounting, effects will be discounted at a rate of 1.5% and costs at 4% per year [33]. Results will be presented with 95% confidence intervals.

The incremental cost-effectiveness ratio of HA versus conservative treatment will be expressed in a cost-utility ratio, i.e., in terms of cost per Quality-Adjusted Life Years (QALY). Cost-utility ratios will be calculated by dividing the difference in mean costs of the two interventions by the difference in their mean effects. Policy makers and healthcare economists have proposed that costs varying from € 25,000 up to € 75,000 (US$ 31,600 - US$ 94,700) per QALY may be considered as acceptable [34,35].

In addition to the outcome variables mentioned above, the following data will be collected:

a) Intrinsic variables (baseline data): dominant side, age, gender, American Society of Anesthesiologists (ASA) grade, alcohol and tobacco consumption, comorbidity including osteoporosis, household composition, and medication use

b) Injury related variables: affected side, mechanism of injury, fracture classification (Hertel)

c) Intervention-related variables: surgical delay (i.e., time between fracture and surgery; HA-group only), time between injury and start of physical therapy, days of collar and cuff use, and total number of physical therapy sessions

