**Figure 4 F4:**
[figure not shown]
**Schedule of follow-up measurements**.

Clinical assessments will occur at the time of admission to the hospital (baseline), one week (3-10 days window), three weeks (11-28 days window), six weeks (4-8 weeks window), three months weeks (11-15 weeks window), six months (5-7 months window), 12 months (11-13 months window), and 24 months (24-26 months window) after surgery (HA group) or after start of conservative treatment (conservative group).

At baseline, multiple intrinsic (i.e., patient-related) and injury-related variables will be collected. At the three, six, 12, and 24 months FU visit, an independent researcher will determine the Constant score. In order to prevent bias the Constant score will be determined by an independent assessor. At each clinic FU visit, the researcher will ascertain patient status (i.e., secondary interventions, adverse events/complications, deaths), and will verify information within medical records. At each visit, patients will be asked to complete the questionnaires relating to disability (DASH score), and VAS for pain. From six weeks onwards, SF-36, EQ-5D, and health care consumption questionnaires will also be completed. A postal version of the latter questionnaire will be sent at 18 months in order to minimize recall bias.

As part of standard of care, X-rays of the shoulder will be made at the time of admission to hospital (baseline), at one, three and six weeks, and three and 12 months after surgery (HA group) or start of conservative treatment. CT scans that will be conducted pre-treatment, which are required for correct classification of the fracture, are also part of standard of care. As part of this trial, one additional CT-scan will be made at 12 months FU in order to determine consolidation (i.e. vanishing tubercles).

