### Statistical analysis

The research data will be reported following the CONsolidated Standards of Reporting Trial (CONSORT). Data will be analyzed using the Statistical Package for the Social Sciences (SPSS) version 16.0 or higher (SPSS, Chicago, Ill., USA). Normality of continuous data will be tested with the Shapiro Wilk test, and homogeneity of variances will be tested using the Levene's test. Protocol violations will be recorded; data will be analyzed with and without patients with protocol violation.

Differences in baseline characteristics (i.e., intrinsic and injury-related variables) between both intervention groups will be assessed using the Student's T-test (parametric numeric data), Mann-Whitney U-test (non-parametric numeric data) or Chi-square test (categorical data). Data will be presented as mean ± SD (parametric data) or medians and percentiles (non-parametric data).

Univariate analysis will be performed to test the difference in primary and secondary outcome measures between the intervention groups using the Student's T-test (parametric data), Mann Whitney U-test (non-parametric data) or Chi-square analysis (categorical data).

Multinomial logistic regression analysis will be performed to model the relation between different covariates and the Constant score. Intrinsic and fracture-related variables that display a p-value < 0.5 in univariate analyses will be added as covariate. Similar models will be made to model the relation between covariates and the other outcome measures.

A p-value < 0.05 (2-sided tests) will be taken as threshold of statistical significance.

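### The 12-month Constant score is compared between arms without adjustment, and the uninjured-shoulder score, which the trial collects, has no stated use: a missed precision gain

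*Protocol article*

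**What the plan says.** The Outcome measures section states: "The primary outcome measure will be the Constant score". It gives most of the scale to physical performance: "The objective variables are range of motion (ROM; 40 points) and strength (25 points), which give a total of 65 points". It adds: "The right and left shoulders will be assessed separately".

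The Abstract sets the time point, the aim being to "compare the Constant scores (reflecting functional outcome and pain) at one year". On timing, the Follow up of patients section says: "At the three, six, 12, and 24 months FU visit, an independent researcher will determine the Constant score". No baseline or recalled pre-injury Constant score is scheduled.

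The Statistical analysis section says: "Univariate analysis will be performed to test the difference in primary and secondary outcome measures between the intervention groups". The tests named for a numeric outcome are Student's t and Mann-Whitney. A separate multinomial logistic model relates covariates to the Constant score. It admits intrinsic and fracture-related variables whose univariate p-value is below 0.5. The list of additional data begins: "Intrinsic variables (baseline data): dominant side, age, gender". Neither that list nor the list of injury-related variables contains the uninjured-side Constant score.

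The Background criticises the one earlier randomised trial for "indistinct inclusion criteria and differences in age at baseline".

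**The concern.** Range of motion and strength make up 65 of the 100 points. It is plausible that both vary with age, sex and build in patients aged 65 and over with no upper age limit. A fresh fracture rules out a baseline score on the injured side, so the uninjured shoulder is the nearest stand-in for pre-injury function. The trial already scores that shoulder with the same instrument, but as the analysis is written the result cannot enter the treatment comparison.

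Precision is at stake. An unadjusted test leaves in the error term whatever between-patient variation the uninjured side could explain. With about 30 evaluable patients per arm, chance imbalance in such a characteristic can move the estimate by a visible amount. The protocol faults the earlier trial for age imbalance, yet its own between-arm test does not adjust for age.

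**Working it through.** **Inputs from the Sample size calculation section.** Means 47 and 56, so the difference is 9 points; SD 12 per group; two-sided alpha 0.05; power 0.80; 30 evaluable per group.

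**Input not in the document.** The correlation r between the 12-month injured-side score and the uninjured-side score. I assume 0 to 0.5.

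**1. The plan's own figure.** Normal approximation: n = 2 × (1.96 + 0.84)² × 12² / 9² = 27.9, so 28 per group. The t-test calculation gives 28.9, so 29. The stated 30 is consistent with both and is slightly generous.

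**2. Unadjusted comparison at 30 per group.** Standard error of the difference = 12 × √(2/30) = 3.10. Two-sided t-test power for 9 points = 0.815.

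**3. Adjusted comparison.** A linear model with the uninjured-side score as covariate has residual SD = 12 × √(1 − r²), so the standard error is 3.10 × √(1 − r²). The equivalent gain in sample size is 1/(1 − r²) − 1.

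| assumed r | residual SD | standard error | power for 9 points | equivalent extra patients |
|---|---|---|---|---|
| 0 | 12.00 | 3.10 | 0.815 | 0% |
| 0.1 | 11.94 | 3.08 | 0.819 | 1% |
| 0.2 | 11.76 | 3.04 | 0.830 | 4% |
| 0.3 | 11.45 | 2.96 | 0.849 | 10% |
| 0.4 | 11.00 | 2.84 | 0.876 | 19% |
| 0.5 | 10.39 | 2.68 | 0.910 | 33% |

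These powers use 58 degrees of freedom. Losing one to the covariate changes them by less than 0.001, so almost nothing is lost if r is near zero.

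**4. Chance imbalance, the same gain seen another way.** With 30 per group, a standardised covariate difference of 1.96 × √(2/30) = 0.51 SD lies at the edge of its 95% chance range. It shifts the unadjusted difference by r × 0.51 × 12: about 1.8 points at r = 0.3 and 3.0 points at r = 0.5, against a 9-point target.

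**5. Why a covariate and not a side-to-side difference.** If both sides have SD 12, the difference score has SD 12 × √(2(1 − r)). At r = 0.3 that is 14.2, which needs 40 per group (normal approximation) instead of 28. At r = 0.5 it is 12.0, with no gain. Subtracting the uninjured side can therefore cost power; adjusting for it cannot cost more than a trivial amount.

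**The case against.** **Only a condensed article is at hand.** The purpose of the uninjured-side score, or the version of the Constant score used, could be set out in a fuller document. That stands as far as silence goes. The article names no version, so one cannot say that it rules out a relative or age-adjusted score, and the absence of any stratification factor is no finding. But the article does fix the between-arm test, the source of covariates and the selection rule, and as fixed these leave the uninjured side out. It is also a natural reading, not an explicit statement, that both shoulders are scored at every Constant visit.

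**Age and gender are not ignored.** They are candidate covariates at a liberal threshold. This stands, and it shrinks the possible gain: what matters is the correlation left after age and gender. But the model that may contain them is described as relating covariates to the score. It is separate from the test of treatment, and entry depends on the data. Whether a multinomial logistic model suits a 0 to 100 score is a separate question.

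**Stronger readings a reader might infer.** One is that the lack of a pre-injury reference biases the result. It does not: allocation is random, and patients with impaired shoulder function before the injury are excluded. Another is that the unadjusted analysis leaves the trial underpowered. At the planned 30 evaluable per arm, power is 0.815 against a target of 0.80. If the 10% mortality and 20% loss are added, 40 × 0.70 = 28 remain and power is 0.787, but that concerns the attrition allowance, not adjustment. A third is that the uninjured side would remove the noise from age, sex and strength. It can only reduce it, by an amount that the document does not let one calculate.

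**Feasibility.** Patients are approached in the Emergency Department with an acute fracture, so a pre-allocation assessment of the other arm may be incomplete. This stands and is dealt with in the fix.

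**Conclusion.** The point holds as a missed precision gain. The primary comparison is fixed as unadjusted, and a closely related measurement that the trial already takes has no stated role. No stated figure is wrong: the sample size reproduces, and the unadjusted test is valid under randomisation.

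The size rests wholly on an assumed between-side correlation. Across r = 0.1 to 0.5, power for 9 points rises from 0.815 to between 0.819 and 0.910. It is negligible at the low end, worth about 10% more patients at r = 0.3, and worth a third more at r = 0.5. It is smaller to the extent that age and gender already carry that correlation. The change is worth making because the likely gain is modest but the statistical cost is close to nil.

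**What to change.** In the Statistical analysis section, make the primary comparison a linear model of the 12-month injured-side Constant score on treatment. Fixed covariates would be the uninjured-side Constant score taken before allocation, age and gender. All three should be named in advance and kept whatever their univariate p-values. Report the adjusted difference with its 95% confidence interval.

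Add an uninjured-side Constant assessment to the baseline schedule, before allocation, with the same goniometer and spring balance. Where that value is missing, impute the mean of the covariate over all randomised patients. Do not substitute the 3-month value: it is post-randomisation, use of the other arm by then could differ between treatments, patients lost earlier would have none, and it would mix two kinds of measurement in one covariate.

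State in the Outcome measures section which version of the Constant score is primary and what the uninjured-side score is for. A score expressed as a percentage of the uninjured side should be a supporting endpoint at most, since it is noisier where the other shoulder is poor.

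The cost is one short extra assessment before allocation, which some acutely injured patients may not complete, and a few sentences of analysis text. No extra enrolment is needed.
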